**Fig. 1 Fig1:**
[figure not shown]
2 × 2 factorial design. Using a 2 × 2 factorial design, this study will evaluate the effect of community-based mentor mothers (cMMs), text messaging, or both on service utilization and maternal and child health outcome indicators

The interventions will be added to fully integrated high-quality HIV and antenatal, maternal, neonatal, and child health (ANC/MNCH) services already offered at these sites. These services will be enhanced with regular Continuing Medical Education seminars and customer care/stigma-reduction training for health workers.

### Participants

We aim to enroll 1336 HIV-infected pregnant women identified in the ANC clinics at study sites. We are including HIV-infected pregnant women who are 18 years or older, have access to a mobile phone (and have disclosed their HIV status to any person sharing the phone), and are willing to have home visits (or meetings with a cMM in an alternate location). We are excluding non-pregnant women, those with unknown HIV status, or those uninfected at the time of the first ANC visit. Approximately 334 women will be enrolled in each of the four study arms. HIV-positive pregnant women attending ANC clinics at one of the study sites will be recruited by a study nurse at presentation to clinic or referral from the community. Informed consent will be obtained for all participants. Women will be sequentially recruited until the sample size has been attained.

### Interventions

Our interventions build on comprehensive integrated HIV and ANC/MNCH services at the clinic level, adding evidence-based approaches in the community and at the individual level to support adherence to and retention in the setting of Option B+. These include (1) cMMs who conduct home visits and other community outreach activities to support PMTCT services and (2) theory-based mobile phone text messages with bi-directional communication to relay health messages and help retain women, men, and infants in existing clinical services.

#### cMMs

cMMs are women living with HIV with recent pregnancy experience who support uptake and retention of PMTCT services in their communities. Unlike traditional facility-based mentor mother programs, in this study, cMMs will be based in the community and will conduct home visits for HIV-positive women (together with their male partners if desired) in their respective communities in order to assist with safe disclosure, support safe infant feeding, promote safer sex and family planning, encourage early infant testing and follow-up, and promote ART adherence and return for HIV care visits.

Criteria for selecting cMMs are modeled on Kenya Mentor Mother Program Guidelines [20]. These include being an HIV-positive mother, having recent PMTCT experience (6 months–2 years), attaining a minimum of Standard 8 education, having disclosed HIV status to at least one person within her household, living within the local community, and demonstrating good ART adherence for at least 6 months. cMMs will participate in 2 weeks of initial training that covers basic medical knowledge about HIV infection and ART, behaviors that help prevent mother-to-child transmission, safer feeding options for infants, counseling methods that can help women to safely disclose their status, strategies for negotiating safer sexual practices, and nutritional guidelines for women living with HIV as outlined in the Kenya Mentor Mother National Guidelines [20]. This training will include stigma-reduction and sensitivity training modules.

For this study, the home locations provided by the enrolled pregnant women will be grouped into zones. Each zone will comprise approximately 10 villages and will correspond to the geographic sub-locations in the community unit. Each zone will be given a unique identifying number and will have two to three resident cMMs who will also be identified by that number. The research staff will obtain informed consent from the HIV-positive woman for home visits by the cMM. Women who do not wish to be visited at home but who accept meetings with cMMs will be given the option to meet at an alternate location. Each cMM will be initially assigned 25–30 women, whom she will follow through pregnancy and 12 months postpartum. The cMM visit schedule is designed to coordinate with ANC visits, maternal clinic visits, and infant HIV testing and immunization schedules to maximize retention in PMTCT and other essential health services for women and children as outlined in the national community maternal newborn health (CMNH) guidelines for Kenya. Specifically, cMMs will conduct at least two prenatal visits 4 weeks apart, one visit on the day of delivery (day 0) and additional postnatal visits on days 2 and 7, weeks 6, 10, and 14, and at months 6, 9, and 12. During home visits, cMMs will provide HIV and other health education, support HIV disclosure and ART adherence, and facilitate retention in care. To assist with their duties, cMMs will each be given a bicycle, identifying study T-shirts, a mobile phone, a CMNH counseling chart, basic supplies, and an initial basic monthly allowance of about $117 USD. A full-time study nurse will perform day-to-day supervision of cMM activities in each study zone.

#### Mobile phone text messaging

Previously tested text messages sent antenatally through 6 weeks postpartum in this setting were adopted from Odeny et al. [23, 24]. We conducted additional focus group discussions to refine the content, optimum frequency, and timing of the additional text messages to be used in this study, focusing on ART adherence and retention in care for Option B+ [28]. Based on focus group input, HIV will not be explicitly mentioned in text messages. However, medication adherence will be emphasized along with reminders for return clinic visits and general health messages. Participating women will receive text messages at their preferred frequency and in their preferred language (from a choice of English, Kiswahili, or Dholuo). Women who share phones will be enrolled only if they have disclosed their HIV status to the person with whom the phone is shared. From our previous work with mobile technologies for HIV prevention and treatment, we have developed an automated text messaging software that allows customization of messages based on an individual recipient’s preferred language and preferred time for receiving messages. Further individual tailoring allows options for messages to include a participant’s name as well as her infant’s name and sex after delivery. Participants’ phone numbers and text preferences will be recorded by sending a text message from their mobile phone to our automated software using a pre-defined syntax. The syntax will include their unique study identification number, date of the last normal menstrual period, preferred language, a preferred time for receiving texts, and an option to provide a preferred name. Participants’ mobile phones will be loaded with 20 Kenya Shillings (approximately $0.20 USD) worth of airtime to cover the cost of this registration message. After registration, our automated study software will send out free messages weekly, at the preferred time of day and in the language specified by the participant. Weekly message content is intended to coincide with PMTCT care and maternal child health schedules and is sent through 1 year postpartum. A bi-directional communication component will supplement the automated text messages to provide additional support and education for women. At any time during the study, participants will be allowed to call or send a text to the study coordinator, a nurse trained and experienced in PMTCT and maternal and child health. Participants will be able to request to talk with the study coordinator by sending a free “call back” message. Whenever a participant requests to be called back, our study software will immediately send back a confirmation response and simultaneously send a text message to alert the study coordinator. The coordinator will then call the patient and record details of their conversation.

### Study procedures

On-the-job training to strengthen the delivery of fully integrated ANC/MNCH/HIV clinical services will be conducted. Refresher trainings for health care providers at study sites will cover the components of high-quality ANC, PMTCT, and HIV treatment for pregnant women; early infant diagnosis; care and treatment for HIV-exposed infants and HIV-infected children; and postpartum family planning.

Study interventions will begin during pregnancy when the participant is enrolled and continue up to12 months postpartum. Blood sampling and laboratory testing required for primary and secondary study outcomes, including HIV testing for pregnant women and exposed infants, maternal CD4 counts, and viral loads, will be conducted as part of routine care per Kenya National ART guidelines by health facility staff.

We will also establish a Community Advisory Group (CAG) composed of local health workers, community leaders, representatives of community groups, and persons living with HIV in the study communities. This group will be invited to participate in a multi-day workshop to discuss the study plans, refine the content of community outreach messages, and discuss the cMM intervention; as well as in regular meetings throughout the study period. We will work with the CAG to develop methods for introducing the study, obtaining local support, and keeping communities informed about study progress and results.

### Data collection and measures

Standardized HIV clinic visit forms and clinic registers developed by the Kenyan Ministry of Health (MOH) are used at all patient clinic visits. For this study, a standardized electronic data abstraction form with built-in quality controls has been developed to capture demographic and clinical information from these clinic and patient records. Data will be collected by trained research staff from source documents on a weekly or bi-weekly basis. All participant visits since the last data abstraction will be entered into the electronic form. Research staff will support accurate and thorough documentation by health care providers during routine site visits. Data collection on study participants will continue for a minimum of 12 months postpartum or until study end.

Primary outcome measures include adherence to ART and retention in care at 12 months postpartum. ART adherence will be measured via self-report routinely collected in the woman’s medical record and viral load. Patient adherence is classified by MOH routine data collection tools as good (>95%), fair (85–94%), or poor (<85%) assessed from the last clinic visit, with clear definitions for each of these categories. Viral load measurements will be conducted as per Kenya National ART guidelines after 6 months of ART for those newly initiating (or at time of pregnancy identification for those already on ART). Those with viral load < 1000 copies/mL will be considered virally suppressed. Those with viral load > 1000 copies/mL will be evaluated for evidence of treatment failure or poor adherence. Our primary outcome for retention in care will be obtained from the women’s clinic visit history and is defined as the proportion of women who have an HIV care visit within 90 days at 12 months after delivery. Data will be shared in agreement with funder (National Institutes of Health, NIH) data sharing policies. Results will be disseminated to local stakeholders (including participants) through local presentations, regional/national/international conferences, and publications.

### Power and sample size estimation

We have powered this study based on differences in proportions in a cluster randomized trial for our key outcomes of maternal ART adherence (percentage of women who report at least 85% adherence) and maternal retention in care (proportion of women with visit within 90 days) at 12 months postpartum. Our sample size and power estimates are based on both clinical and logistic factors. Current estimates on required adherence to non-nucleoside-based regimens are estimated to be 75–80% [29–31]. Additionally, current standard HIV clinic forms in use in Kenya define good adherence as > 95% adherence, fair adherence as 85–94% adherence, and poor adherence as < 85% adherence based on number of missed doses. Power calculations were made based on estimated differences in these rates in the intervention versus the control arms of the study, using appropriate methods for clustered data [32]. We estimated a baseline ART adherence rate of 55% based on current rates found in the literature for sub-Saharan Africa [33] and a baseline retention in care rate of 48% based on data from our recent trial of service integration conducted in the same region in Kenya [26]. We powered our study to be able to detect a 25% absolute increase in ART adherence due to each intervention individually. Given that the actual intracluster correlation coefficients (ICCs) are not known for these outcomes and are not easily specified, we calculated the number of communities needed for ICCs ranging from 0.06–0.12 for 80% power with a two-sided alpha of 0.05, for a fixed average cluster size (Table 1). To achieve 80% power for detecting a significant difference in the proportion who are at least 85% adherent at 12 months, from 55% in the control arm versus 80% in the intervention arm (two-sided *p* < 0.05), with a conservative (high) ICC of 0.12 and an average of 70 women sampled per community (an estimated minimum of 50 and maximum of 130 women per cluster), we would need 18 communities, 4.5 in each arm of the trial. For retention in care, to achieve 80% power to detect a significant difference in the proportion who have an HIV care visit within 90 days of the 12 months postpartum date, from an estimated 48% in the control arm versus 73% in the intervention arm (two-sided *p* < 0.05), with a conservative (high) ICC of 0.12 and an average of 70 women sampled per community (50—130 women per cluster), we would need 20 communities, 5 in each arm of the trial. This sample size will power us to evaluate both of our primary outcomes. It is conservative due to the high ICC estimate and thus should also be sufficient if we experience loss to follow-up. This will result in a target sample size of 1336 women (334 women per arm).

**Table 1 Tab1:** Sample size calculations with different levels of intracluster correlation coefficient (ICC)^a^

Adherence (proportion of women at least 85% adherent at 12 months postpartum)					
ICC	Control	Difference	Intervention	Number of sites	Total sample
0.06	55%	25%	80%	10	680
0.07	55%	25%	80%	12	772
0.08	55%	25%	80%	12	866
0.09	55%	25%	80%	14	958
0.10	55%	25%	80%	16	1050
0.11	55%	25%	80%	16	1144
0.12	55%	25%	80%	18	1236
Retention in care (proportion of women with an HIV visit within last 90 days at 12 months postpartum)					
ICC	Control	Difference	Intervention	Number of sites	Total sample
0.06	48%	25%	73%	10	734
0.07	48%	25%	73%	12	834
0.08	48%	25%	73%	14	934
0.09	48%	25%	73%	14	1036
0.10	48%	25%	73%	16	1136
0.11	48%	25%	73%	18	1236
0.12	48%	25%	73%	20	1336

^a^Estimates adjusted for unequal cluster sizes, assuming an average cluster size of 70

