### Primary analyses

Preliminary analyses will summarize characteristics of the intervention and control women and assess frequency distributions of variables to identify outlying or unusual values. Initial analyses of our primary outcomes of maternal ART adherence and maternal retention in care (dichotomous variables) will be based on comparisons of proportions between intervention and control groups using cluster-adjusted chi square tests. Although there are only 24 clusters, each mean or percentage will be based on a relatively large number of women, and the normal approximation to the binomial distribution can be used. These tests will be evaluated based on a two-sided alternative hypothesis with a 5% type I error rate. Given the clustered study design, generalized estimating equation (GEE) models will be used to test for differences of interest in univariate and multi-variable models, adjusted for relevant covariates (such as time on ART), using logistic links for these binary outcomes. Secondary outcomes, such as time to infant testing uptake, maternal viral load suppression, and changes in maternal CD4 counts, will be analyzed using similar methods, taking into account the nature of the dependent variable (continuous, dichotomous, or time to event). Results will be summarized as odds ratios for models based on binary responses (e.g., enrollment in HIV care), hazard ratios for time-to-event outcomes (e.g., time to infant HIV test), and mean changes for continuous responses (e.g., maternal CD4 count); respective 95% confidence intervals will also be reported based on the robust variance estimates from the GEE models.

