## Discussion

This study will determine the impact of long-term (up to 12 months postpartum) text messaging and cMMs on retention in and adherence to ART among pregnant and breastfeeding women living with HIV in Kenya. It will address key gaps in our understanding of what interventions may successfully promote long-term retention in the PMTCT cascade of care. While support among women living with HIV appears to be high for Option B+, high rates of “non-starters” (women who default after first visit) and losses of up to a third of women on ART are concerning [36–39]. The full benefits of Option B+ can only be realized if women are adherent to ART during pregnancy, breastfeeding, and throughout life.

Community-based strategies have the potential to enhance adherence and retention. Most countries in sub-Saharan Africa utilize community or lay health workers to support HIV services. However these workers may or may not be people living with HIV (PLHIV), and the majority are facility-based. While this has its benefits, the WHO and UNAIDS strongly recommend involvement of PLHIV in their own care [40]. Models utilizing PLHIV to support HIV services, such as peer navigators or the Mother-to-Mother program specifically for PMTCT, have shown some benefit but require rigorous evaluation. Our study will be able to determine the separate and combined effectiveness of cMMs and text messages specifically for women on Option B+.

In Kenya, a country of 43 million people, there are currently 37.8 million active mobile phone subscriptions, representing about 88% of the population [41]. While access to a mobile phone is significantly associated with postpartum retention in PMTCT [42–44], there are few studies evaluating the long-term impact of mobile phone technologies on improving long-term retention and adherence in the context of Option B+. One cluster randomized trial of text messages to support PMTCT care in Kenya did not demonstrate increased uptake of PMTCT services such as ART uptake, facility delivery, or infant testing, but it did not study the effects long term [45]. Another recent randomized trial in Kenya used behavior-based text messaging to improve uptake of early infant diagnosis and postnatal retention [23]. Our study will build on the results of this successful trial by using theory-based behavior text messaging to support long-term adherence and retention in the context of Option B+.

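### The 80% power is a two-group (factorial-margin) figure, but it is stated for standard-of-care control rates and a 25-point gain from each intervention alone

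*Protocol article*

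**What the plan says.** The trial is a 2 × 2 factorial with 24 sites, six per arm, and 1336 women, 334 per arm (Protocol article, Study design and Participants).

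Power and sample size estimation states the target: "We powered our study to be able to detect a 25% absolute increase in ART adherence due to each intervention individually". Adherence is to rise "from 55% in the control arm versus 80% in the intervention arm", and retention "from an estimated 48% in the control arm versus 73% in the intervention arm". The 55% and 48% are introduced as baseline rates, taken from the literature and from an earlier trial in the same region. Sizing is "for 80% power with a two-sided alpha of 0.05, for a fixed average cluster size", "with a conservative (high) ICC of 0.12". For retention the result is that "we would need 20 communities, 5 in each arm of the trial"; for adherence it is 18 sites, or 4.5 per arm. Table 1 has one control column and one intervention column.

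Primary analyses plans "comparisons of proportions between intervention and control groups using cluster-adjusted chi square tests", followed by GEE models with a logistic link. The Discussion says: "Our study will be able to determine the separate and combined effectiveness of cMMs and text messages specifically for women on Option B".

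**The concern.** In a four-arm factorial trial, the words control and intervention can mean two things. They can mean the standard-care arm against one single-intervention arm, or the two margins of one factor. The control rate and the number of women differ between the two. The sample size section appears to take its rates from the first and its sample size from the second. If so, the stated power belongs to neither comparison as described.

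Two things are at stake. A single-arm result that is not significant could be read as coming from a comparison with 80% power. And the effect that the main comparison can detect would differ from the one stated. The Primary analyses section does not settle which contrast is meant.

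**Working it through.** **1. Reproduce Table 1.** Inputs from the sample size section: two-sided alpha 0.05, power 80%, the rates above, mean cluster size 70 with range 50–130, ICC 0.06–0.12. Two inputs are inferred, not stated: a continuity correction, and a coefficient of variation of ((130 − 50)/4)/70 = 0.286.

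- n per group without clustering = [1.96√(2p̄(1−p̄)) + 0.842√(p₁(1−p₁)+p₂(1−p₂))]²/d², where d = p₂ − p₁. This gives 53.9 (adherence) and 58.8 (retention).
- With the continuity correction, n/4 × [1+√(1+4/(nd))]²: 61.6 → 62 and 66.6 → 67.
- Design effect = 1 + (70(1+0.286²) − 1) × 0.12 = 9.966.
- Total for two groups: 2 × 62 × 9.966 = 1236 (stated 1236) and 2 × 67 × 9.966 = 1335 (stated 1336).

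All 14 rows of Table 1 match within 2 women. The site counts are all even, but some do not divide by four, hence 4.5 per arm. So 1336 is a two-group total, 668 v 668. For a single arm against standard care, the same method needs 618 or 668 women per arm, that is 2471 or 2671 over four arms.

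**2. Rates at the margin.** Suppose each intervention alone reaches the planned rate, and b is the combined-arm rate.

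- Comparator margin: (55+80)/2 = 67.5% and (48+73)/2 = 60.5%.
- For a 25-point marginal effect, (80+b)/2 − 67.5 = 25 gives b = 105% for adherence. The same equation for retention gives b = 98%.
- No interaction on the logit scale, adherence: odds ratio 4.00/1.222 = 3.27, combined odds 13.09, b = 92.9%, margins 67.5% v 86.5%, difference 19.0 points.
- No interaction on the logit scale, retention: odds ratio 2.704/0.923 = 2.93, combined odds 7.92, b = 88.8%, margins 60.5% v 80.9%, difference 20.4 points.
- If the combination adds nothing, b = 80% or 73%, and the difference is 12.5 points.

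**3. Power.** Power = Φ{[d√n′ − 1.96√(2p̄(1−p̄))]/√(p₁(1−p₁)+p₂(1−p₂))}, with n′ = women per group divided by the design effect. With the continuity correction, n′ is multiplied by (1 − 1/(n′d))². With 24 sites the mean cluster is 1336/24 = 55.7, and the design effect at ICC 0.12 with the same coefficient of variation is 8.11. Each margin is treated as one group at its mean rate, which is an approximation.

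At ICC 0.12 (lower figure with, upper figure without the continuity correction):

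| Contrast | 55.7 per site | 70 per site |
|---|---|---|
| Margin, no logit interaction, adherence (19.0 points) | 78–83% | 68–75% |
| Margin, no logit interaction, retention (20.4 points) | 78–83% | 68–74% |
| Margin, combination adds nothing, adherence (12.5 points) | 38–45% | 30–38% |
| Margin, combination adds nothing, retention (12.5 points) | 34–40% | 27–33% |
| Margin, fully additive retention (25 points) | 94–96% | 88–91% |
| Single arm v standard care, adherence (25 points) | 59–68% | 49–59% |
| Single arm v standard care, retention (25 points) | 56–65% | 45–56% |

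Example for the single arm, adherence, 70 per site, uncorrected: n′ = 334/9.966 = 33.5; (0.25 × 5.79 − 1.298)/0.638 = 0.23; power 59%.

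A t reference on 10 degrees of freedom puts the single-arm contrast at about 45–58% at ICC 0.12. At ICC 0.06 that contrast has about 72–91% across all variants.

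**4. Interaction.** The detectable difference of differences is 2.80 × √(Σp(1−p)/n′) over the four arms. With n′ = 334/8.11 = 41.2, it is about 35–40 points at ICC 0.12, for b between no logit interaction and no added benefit.

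**The case against.** The strongest reply is that no passage says a single arm will be tested against standard care. A two-group total is the usual basis for a factorial analysed at its margins. Table 1 has two columns, and the analysis text refers to all 24 clusters. On that reading the per-arm figures merely divide the total by four, and a 25-point marginal difference from 55% or 48% would have 80% power or more by the protocol's own method. This stands in part. A reader might infer that the trial's real comparison is 6 v 6 sites and that it is therefore underpowered, or needs about 2670 women. The documents do not support that, because they leave the contrast open and their arithmetic points to the margin. The reply does not rescue the rates, however: 55% and 48% are standard-of-care figures, and neither margin consists only of women under standard care.

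A reader might also infer that the planned effects are impossible for both outcomes. They are not: additive effects give 98% for retention. The protocol assumes no additivity for adherence either, and on the logit scale both outcomes stay below 100%.

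The single-arm shortfall also depends on ICC 0.12, which the protocol calls conservative; at 0.06 much of it disappears. But 0.12 is the value that set the sample size, and the same section relies on it to absorb loss to follow-up.

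Finally, model parameterisation and the ranking of contrasts may sit in an analysis plan that is not shown, so the lack of a stated interaction test is not raised here. The Discussion sentence is an aim, not a power claim. What remains is the power statement itself, which the article does make.

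**Conclusion.** The point holds as a mismatch between the stated power and the comparison it is attached to. The sample size is that of a factorial margin; the rates are those of standard care against a single intervention. For adherence, no reading gives the stated power for the stated effect at the design ICC. For retention, the marginal reading works only under full additivity, which is not stated.

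At ICC 0.12 and without logit interaction, the main-effect comparison is near its target with 55.7 women per site (78–83%) and below it at the planning cluster size (68–75%), for differences of about 19–20 points. If the combination adds nothing, power is about 27–45%. A single arm against standard care has about 45–68%, or 72–91% at ICC 0.06.

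These figures rest on the inferred continuity correction and cluster-size variation, which the match to every row of Table 1 supports, and on each intervention alone reaching the planned 80% or 73%. They do not show that the design is unsound or too small for its main effects.

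**What to change.** - State that the primary contrast for each intervention is its main effect over all 24 sites, from a GEE with both factors in the model.
- Restate power for the marginal rates, with an explicit interaction assumption and the ICC and cluster size used. Without logit interaction these are 67.5% v 86.5% and 60.5% v 80.9%.
- Label single-arm-v-standard-care, combined and interaction estimates as secondary. Give their lower power: about 45–68% for 25 points at ICC 0.12, and a detectable interaction of about 35–40 points with 55.7 women per site.
- Align the Discussion sentence on separate and combined effectiveness with this.

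The cost is a change of wording in three sections, with no extra women or sites. The downside is that the stated figures become less favourable. Trial status reports month 44 of 60, so the contrast should be fixed before outcome data are analysed.
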